# Cardio-Cerebral Protective Effect of Moxibustion on Phlegm-Dampness Type Hypertension: Protocol for a Randomized Controlled Trial

**DOI:** 10.2196/79158

**Published:** 2025-12-29

**Keywords:** hypertension, blood pressure, moxibustion, acupoint specificity, cardioprotection, moxibustion, treatment, patients, trials

## Abstract

**Background:**

Hypertension is associated with a high rate of disability and mortality and leads to a substantial socioeconomic burden. Moxibustion is an external treatment in traditional Chinese medicine that has been used to treat mild to moderate hypertension in individuals with phlegm-dampness constitution and has demonstrated acupoint specificity. However, a standard large-scale randomized controlled trial is still needed to verify its effectiveness. This study is proposed to examine the clinical effectiveness and potential cardioprotective benefits of moxibustion performed at home as a treatment for individuals with phlegm-dampness hypertension.

**Objective:**

The objective of this trial is to evaluate the cardio-cerebral protective clinical efficacy of moxibustion for phlegm-dampness type hypertension and to explore its acupoint specific effects.

**Methods:**

This study is a multicenter, randomized controlled trial. A total of 120 patients with mild to moderate hypertension and phlegm-dampness constitution will be recruited and randomly assigned in a 1:1 ratio to the treatment group (acupoint: Zusanli, ST36) or the control group (acupoint: Xuanzhong, GB39). All patients will receive 12 weeks of treatment and a 12-week follow-up period. The primary outcome measure is the change in morning systolic blood pressure from baseline to week 12. The secondary outcome measures include blood pressure–related indicators (morning diastolic blood pressure, average systolic blood pressure, average diastolic blood pressure, nighttime systolic blood pressure, nighttime diastolic blood pressure, and blood pressure circadian rhythm) and short-term blood pressure variability coefficient, all of which will be measured by 24-hour ambulatory blood pressure monitoring. Additionally, cardiac-related indicators measured by 24-hour Holter monitoring, metabolic disorder-related indicators, liver and kidney function indicators, transformed scores of the traditional Chinese medicine phlegm-dampness constitution scale, and the Montreal Cognitive Assessment will also be evaluated.

**Results:**

This study was registered on July 5, 2024, with the Chinese Clinical Trial Registry. Data collection began in June 2023 and ended in February 2025. Currently, data from this trial are in the collection phase, and no data analysis has been performed. As of January 2025, we have collected data from 118 patients. The results of this trial are expected to be submitted for publication in May 2026.

**Conclusions:**

This multicenter, randomized, controlled clinical trial will provide evidence on the clinical effectiveness and potential cardioprotective benefits of moxibustion performed at home as a treatment for individuals with phlegm-dampness type of hypertension.

**Trial Registration:**

Chinese Clinical Trial Registry ChiCTR2400086582; https://www.chictr.org.cn/showproj.html?proj=211688

**International Registered Report Identifier (IRRID):**

DERR1-10.2196/79158

## Introduction

### Background

Hypertension is a chronic disease characterized by persistently elevated arterial blood pressure in the systemic circulation. It is a major risk factor for premature death, stroke, ischemic heart disease, and other cardiovascular and renal diseases globally [1]. Hypertension imposes a substantial global health burden [2], affecting approximately one-third of adults, with only up to 54% receiving a diagnosis [3]. China is among the countries with the highest increase in hypertension prevalence and the lowest control rates. In 2018, the prevalence of hypertension among Chinese adults was 27.5%, whereas the control rate was only 15.3% [4]. Poor long-term blood pressure control can cause irreversible damage to multiple target organs, including the heart, brain, kidneys, and blood vessels, leading to increased disability and mortality rates. Therefore, early intervention is crucial to slow the progression of hypertension and reduce the associated social and economic burdens.

Currently, the primary approaches for hypertension treatment include lifestyle modification and medications. The medication adherence of hypertensive patients in China is only 42.5% [4], far lower than the average level in Asian countries, which is a significant factor contributing to low blood pressure control rates [5], increasing the risk of cardiovascular and target organ damage [6], and negatively impacting patients’ quality of life [7]. Thus, there is an urgent need to develop a treatment method that can maintain stable blood pressure with high safety, good adherence, tolerability, and cost-effectiveness.

Moxibustion, a traditional Chinese medicine (TCM) therapy, uses thermal effects, infrared radiation, photobiochemical effects, and bioelectric effects produced by burning mugwort to stimulate specific acupoints and meridians, thereby dredging meridian, promoting blood circulation, and regulating the body’s neuroendocrine-immune functions [8]. Compared with medication alone, the additional application of moxibustion can effectively control blood pressure [9], correct imbalanced body constitutions [10], and significantly alleviate related symptoms, such as dizziness, headache, and insomnia [11]. Moxibustion is characterized by rapid onset, stable efficacy [12], improved cognitive function [13], and fewer side effects with high safety [11]. Its mechanism of action is multifaceted and multitargeted [13].

Our previous studies indicate the acupoint specificity of moxibustion’s antihypertensive effects [14-16], with differential activation of arcuate neurons depending on the targeted acupoint. Specifically, nerve input at Zusanli (ST36) is greater than that at Xuanzhong (GB39) [17-19]. Clinical trials have shown that moxibustion at Zusanli can significantly reduce 24-hour average systolic blood pressure and improve myocardial oxygen consumption, whereas moxibustion at Xuanzhong shows no significant effect [15]. Although we have confirmed the efficacy and acupoint specificity of moxibustion in treating hypertension, a standard large-sample clinical trial is still needed.

### Objective

We designed this multicenter randomized controlled trial (selecting Zusanli [ST36] as the treatment group and Xuanzhong [GB39] as control group) to provide clinical evidence for the acupoint specific effects of moxibustion on hypertension and its protective effects on the heart and brain.

## Methods

### Ethical Considerations

This study protocol was approved by the Ethics Committee of the Shanghai Tongji University-affiliated Oriental Hospital (2023 research review: 145), the Shanghai University of Traditional Chinese Medicine-affiliated Longhua Hospital (2024LCSY161), and the Shanghai Acupuncture and Meridian Research Institute (2023-169). Written informed consent was obtained from all participants prior to the study and data publication. All study-related examinations and treatments will be provided to participants free of charge. No additional compensation will be offered. The study was registered on July 5, 2024, with the Chinese Clinical Trial Registry (ChiCTR2400086582). All participants will be provided with detailed study information and must provide written informed consent prior to enrollment. The trial results will be submitted for publication in a peer-reviewed journal. Neither patients nor the public were involved in the study's design, conduct, reporting, or dissemination plans.

### Case Selection

Participants in this trial are outpatients receiving treatment between June 2023 and February 2025 at the Oriental Hospital affiliated with Tongji University, Longhua Hospital affiliated with Shanghai University of Traditional Chinese Medicine, and the Shanghai Research Institute of Acupuncture and Meridian. All patients are recruited and screened based on the inclusion and exclusion criteria outlined in the study.

### Inclusion Criteria

In this study, the inclusion criteria are as follows: (1) patients diagnosed with grade 1 or 2 hypertension according to the “Chinese Guidelines for the Prevention and Treatment of Hypertension” (2018 revision) [20] (Multimedia Appendix 1); (2) patients with phlegm-dampness constitution according to the “Classification and Determination of TCM Constitution” (ZYYXH/*t* 157-2009) [21] (Multimedia Appendix 2); (3) age between 18 and 75 years, regardless of sex (male or female); (4) no contraindications to moxibustion: (5) without secondary hypertension, hyperthyroidism, or without severe heart conditions (eg, atrial fibrillation and moderate valvular heart disease), and not being in the unstable phase of angina pectoris or myocardial infarction, not being in the acute phase of stroke, and no malignant diseases; and (6) willingness to participate in the study and to sign the informed consent form.

### Exclusion Criteria

In this study, the exclusion criteria include the following: (1) patients with severe mental disorders (eg, depression, anxiety, or schizophrenia), or with severe conditions requiring hospitalization or interventions; (2) pregnant or breastfeeding women; (3) patients with severe heart, brain, liver, or kidney diseases; and (4) patients unable to tolerate and to persist with moxibustion treatment.

### Elimination Criteria

Participants who do not adhere to the study requirements during the trial, and those who do not meet the inclusion criteria after enrollment, will be removed from this study.

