### Dropout Criteria

In this study, the dropout criteria include the following: (1) participants who meet the inclusion criteria but do not complete the trial or who withdraw midway for various reasons; (2) participants who do not follow the prescribed treatment plan or who receive other treatments or medications that interfere with the assessment of efficacy; and (3) participants who are lost to follow-up or die before completing the trial.

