#### Treatment Group

Participants in the treatment group will receive moxibustion at Zusanli (ST36). All participants will undergo training by professionals on acupoint location, moxibustion techniques, and precautions before beginning treatment. Only patients who pass the training and evaluation will be allowed to perform moxibustion at home, 3 times a week for 12 weeks. The first moxibustion session will be conducted under professional supervision in the clinic, with the skin temperature at the moxibustion site recorded before and after the session. Subsequently, participants will document each moxibustion session with photographs and will complete a moxibustion record form, noting the date, duration, and any adverse reactions. Researchers will conduct 2 random follow-up visits per week to remind participants to complete their moxibustion sessions on time and to verify the frequency, location, duration, and completion of the sessions using photos and record forms. Participants will also undergo outpatient evaluations every 2 weeks to assess their moxibustion adherence and will receive comprehensive assessments at baseline, week 4, week 12, and week 24.

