### Statistical Analysis

Data analysis of the primary outcome will be based on the full analysis set constructed by the intention-to-treat principle, whereby patients will remain in their original group regardless of contamination. The per-protocol set will also be analyzed using sensitivity analysis for the primary outcome to evaluate whether contamination affects the direction of the effect. The secondary outcomes will also be compared based on the per-protocol set. The need to impute missing values will be determined by the proportion of and reasons for missing data. If imputation is necessary, appropriate methods, such as the last observation carried forward, the “best-worst-case” scenario, and multiple imputation regression modeling, will be chosen according to the distribution of the missing values.

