Potential center effects will be statistically addressed through mixed-effects modeling, notwithstanding standardized central screening and intervention procedures. For primary continuous outcomes, linear mixed-effects models will incorporate the treatment group as a fixed effect and center as a random effect, with center-specific random intercepts accounting for recruitment-related heterogeneity. Secondary outcomes will be analyzed using analogous generalized linear mixed models. The primary analysis will use an intention-to-treat approach. The changes in the primary outcome and other secondary outcomes will be compared by using a linear mixed-effects model with group-by-time point interaction (baseline to week 12). For outcomes measured at multiple time points, a repeated-measures ANOVA will first test for overall group, time, and interaction effects. Upon finding a significant interaction (exact *P* values will be reported), post hoc comparisons will be conducted using a hierarchical adjustment strategy: Benjamini-Hochberg false discovery rate control for the primary outcome across time points and Bonferroni correction for families of secondary outcomes. Sociodemographic and clinical characteristics at baseline will be examined for potential group differences by 2-tailed *t* test or χ^2^ test, with exact *P* values reported. Compliance will be presented using descriptive statistics. The specified significance levels (0.025 for the primary outcome and 0.05 for all other analyses) represent the α thresholds (*P* value cutoffs) for hypothesis testing. All *P* values will be reported per journal style: expressed to two digits (or three if *P*<.01) and as *P*<.001 if below that threshold. Data analysis was conducted with SPSS (version 28.0; IBM Corp).

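### The elimination rule takes randomized participants out of the study whom the intention-to-treat primary analysis promises to keep, and nothing limits that removal to the per-protocol set

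*Protocol article*

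**What the plan says.** Three places in the Methods of the protocol article bear on which randomized participants are analysed.

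- **Elimination Criteria.** The section states that "those who do not meet the inclusion criteria after enrollment, will be removed from this study". The same removal applies to a second group, described as "Participants who do not adhere to the study requirements during the trial".
- **Dropout Criteria, item 2.** Dropouts include "participants who do not follow the prescribed treatment plan or who receive other treatments or medications that interfere with the assessment of efficacy".
- **Statistical Analysis.** The first paragraph says "Data analysis of the primary outcome will be based on the full analysis set constructed by the intention-to-treat principle". It then explains what this means for treatment received outside the assigned arm: "patients will remain in their original group regardless of contamination". The second paragraph repeats: "The primary analysis will use an intention-to-treat approach". The per-protocol set serves as a sensitivity analysis for the primary outcome, to see whether contamination changes the direction of the effect. It is also used for the secondary outcomes. Missing values may be imputed by last observation carried forward, a best-worst-case scenario or multiple imputation.

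**The concern.** The same participants are treated in two ways. Someone who stops home moxibustion, or is found ineligible later, leaves the study under one section and stays in the assigned arm under another. Receiving another treatment is contamination in the ordinary sense, so labelling such a person a dropout also sits uneasily with a promise to disregard contamination.

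What is at stake is the composition of the primary comparison. Adherence and added treatment are events after randomization. They may be related to how blood pressure responds and to the acupoint assigned. If the people concerned leave the primary set, the protection given by randomization is weakened. The per-protocol analysis would then cover nearly the same people as the primary one, so it could not show what contamination does.

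**Working it through.** **1. The rules side by side**

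| Participant | Elimination / Dropout Criteria | Statistical Analysis |
|---|---|---|
| Non-adherent during the trial | Removed from the study; departure from the treatment plan is also a dropout | Kept in the assigned arm |
| Found ineligible after enrollment | Removed from the study | Kept, by intention to treat |
| Receives other interfering treatment or medication | Dropout; what happens to the data is not stated | Kept despite contamination |

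The first two rows conflict as printed. In the third, the conflict is only implied by the label. No section says that removal defines the per-protocol set, or that removed participants and dropouts are still measured at week 12 and analysed as randomized.

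**2. Can removal be related to arm and outcome?** Under Treatment Group and Moxibustion Adherence and Completion, adherence is judged from photographs, logs and a rating of acupoint location. That material shows the acupoint, and so the arm. The Blinding section covers data collectors, outcome assessors and statisticians, but does not say who decides on removal. Under Randomization Method the envelope is opened after enrollment, so a participant found ineligible later may already be allocated. Removal for that reason does less harm if it is judged blind from pre-randomization data, but the Elimination Criteria set no such condition. A link is therefore possible; the article does not establish one.

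**3. The planned headroom.** Inputs from Sample Size Calculation: difference 7.2, SD 3.3, margin 5 mm Hg, one-sided α 0.025, power 90%.

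- Excess over the margin: 7.2 − 5 = 2.2 mm Hg.
- n per arm = 2 × (1.96 + 1.2816)² × 3.3² / 2.2² = 47.3, so 48 per arm and 96 in total.
- The stated 120 does not follow from these inputs alone. It would follow with a 20% loss allowance (48 / 0.8 = 60 per arm). That allowance is my assumption: the visible text states none and the formula is not shown. Nothing here depends on it.

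**4. Illustrative shift from removal.** Let a fraction f of one arm be removed, with a mean change that differs by D from that of those kept. The arm's full mean is (1 − f) × kept + f × removed, so removal shifts the arm mean by f × D. Both f and D are assumed; D is set at one and two planned SDs, and no offsetting removal occurs in the other arm.

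| f | D = 3.3 mm Hg | D = 6.6 mm Hg |
|---|---|---|
| 5% | 0.17 | 0.33 |
| 10% | 0.33 | 0.66 |
| 20% | 0.66 | 1.32 |

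Against 2.2 mm Hg this runs from 0.165 / 2.2 = 7.5% to 1.32 / 2.2 = 60% of the headroom.

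**5. What keeping everyone does.** Suppose all 60 per arm are measured, the SD stays at 3.3, and a fraction of the ST36 arm gains nothing (assumed). The standard error is 3.3 × √(2/60) = 0.6025, and power is Φ(excess / 0.6025 − 1.96).

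| Fraction with no gain | Difference (mm Hg) | Excess over margin (mm Hg) | Power |
|---|---|---|---|
| 0% | 7.20 | 2.20 | 95% |
| 5% | 6.84 | 1.84 | 86% |
| 10% | 6.48 | 1.48 | 69% |
| 20% | 5.76 | 0.76 | 24% |

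Because the test is against a margin, the choice between keeping and removing these participants can decide the result.

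**The case against.** The best defence is that a consistent reading exists. The Statistical Analysis section separates a full analysis set from a per-protocol set, which would be pointless if the non-adherent had already left the former. Elimination and dropout could simply mean the end of participation, or be per-protocol criteria in condensed form, with the detail in a full protocol or analysis plan not shown here. That reading may well be what was intended. But the article does not merely omit a definition: it prints an unqualified removal rule that conflicts with its own primary analysis. The conflict stands until the text says which rule governs.

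Other parts of the defence do hold, and they rule out stronger conclusions that a reader might draw:

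- *That medication changers are removed.* Only the Elimination Criteria speak of removal. The Dropout Criteria give a label and do not say that data are discarded.
- *That the full analysis set cannot be formed.* No section says when removal takes effect or that measurement stops. Table 1 schedules ambulatory monitoring at baseline and week 4 as well as week 12, and the plan provides for missing values.
- *That the training test is a further post-randomization exclusion.* The Control Group section makes training and evaluation identical in both arms. Failing bars home treatment, but is not said to remove anyone from the analysis.
- *That the shift could be 2.0 mm Hg.* This needs 20% of one arm removed with a change 10 mm Hg worse. Such a split alone implies a variance of 0.2 × 0.8 × 10² = 16, above the planned total of 3.3² = 10.9 if that SD describes all randomized patients.
- *That the bias favours ST36.* Both arms receive moxibustion, participant blinding is described, and patients who add medication may have lower pressure at week 12. The direction cannot be derived.

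**Conclusion.** The concern holds as a conflict between printed rules. The Elimination Criteria, and by implication item 2 of the Dropout Criteria, are incompatible with the intention-to-treat primary analysis unless their effect is confined to the per-protocol set, and the article does not confine it. Applied as written, the elimination rule would make the primary comparison conditional on post-randomization events.

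Bias is a risk, not a demonstrated result. The range of about 0.2 to 1.3 mm Hg rests entirely on assumed removal rates, assumed differences and one-sided removal. It shows only that plausible selection is not negligible beside a headroom of 2.2 mm Hg. It would be going too far to say that the primary analysis is in effect a per-protocol comparison, because the article does not show which rule was followed.

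**What to change.** Before any analysis, reconcile the Elimination and Dropout Criteria with the Statistical Analysis section:

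- State that non-adherence, other treatments or medications, and later-found ineligibility define exclusion from the per-protocol set only.
- Analyse all randomized participants in their assigned arm in the full analysis set, using every ambulatory blood pressure value obtained, including any after removal or dropout. Treat values not obtained as missing.
- Report removals and dropouts by arm, with reasons.
- Where any follow-up is still open, continue the scheduled ambulatory monitoring for these participants.

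The cost is mainly wording and recovery of readings already taken. The Results section says that no analysis has been done, so the rule can still be set without knowledge of the results. The same section says that collection ended in February 2025, although it also describes collection as current. If it has ended, the last step is largely moot and readings never taken cannot be recovered. The statistical downside is dilution by non-adherence, with the possible loss of power shown in step 5 of the working.

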### Dropout Criteria

In this study, the dropout criteria include the following: (1) participants who meet the inclusion criteria but do not complete the trial or who withdraw midway for various reasons; (2) participants who do not follow the prescribed treatment plan or who receive other treatments or medications that interfere with the assessment of efficacy; and (3) participants who are lost to follow-up or die before completing the trial.

